#### 2.2.6 Carer and patient recruitment.

Local cardiology teams will identify and approach potential participants during routine, in and out-patient HF appointments. Eligible patients will receive information packs for both them and their carer. Those interested in participation will provide permission to be contacted by the research team for recruitment. During this contact, patients will also signpost the research team to their interested carers. Subsequently, these carers will be contacted by the research team for eligibility screening and recruitment. The collaborating hospital sites cover regions with a range of socio-demographic characteristics (*i.e.,* education level, socio-economic status, and ethnicity), which will maximise the diversity of the recruited sample.

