#### 2.2.8 Intervention design.

HELP design was based on prior literature and comprehensive input from carers of patients with HF and healthcare professionals, with the co-development and feasibility testing of this intervention previously reported in detail [10]. HELP constitutes a six-week, nurse-led, psychoeducational programme comprising two components:

1)
*Online support group sessions*

Nurse-led, weekly online support group sessions are delivered to groups of approximately twelve carers over a six-week period. Each session lasts sixty minutes and is underpinned by a standardised, educational presentation covering the topics displayed in Table 1. Following each educational presentation, the HF nurse facilitates a group discussion to issue tailored advice, guidance, and signposting, along with providing a platform for carers to engage in peer support.

**Table 1 pone.0347037.t001:** Support Group Schedule.

Session Number	Topic	Content
1	Introduction	Group introductions Summary of HELP content Guidance on access and usage of self-directed educational resources (booklet and website)
2	Understanding HF	Overview of HF Symptoms Prognosis Palliative care
3	Personal Wellbeing	Looking after physical and emotional wellbeing Management strategies for complex emotions
4	Communication and Support	Communicating with loved ones and healthcare professionals
5	Practical Skills for Supporting Self-Management	Controlling diet and salt intake Management of fluid and medication Exercise Monitoring symptoms at home
6	Feedback	Discussion of experience and final comments/ questions Feedback on HELP and areas of improvement

**Legend** HELP = HEart faiLure carer support Programme and HF = heart failure.

2)
*Self-directed, educational resources (booklet and website)*

Upon HELP enrolment, carers will receive an educational booklet (S3 Text) and access to a supplementary website. Both resources were co-designed and professionally produced. The educational booklet complements the online support group sessions by facilitating self-directed learning across the following five chapters:

Chapter 1: What is HF?Chapter 2: Planning for the futureChapter 3: Looking after yourselfChapter 4: CommunicationChapter 5: Your role as a carer

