#### 2.2.9 Intervention delivery.

HELP will be delivered by local specialist HF nurses across the collaborating sites. Following recruitment, carers will be assigned a start date for HELP. One week prior to the first online support group session, carers will receive the educational booklet and access to the supplementary website, along with supporting programme materials (*i.e.,* online support group schedule and guidance on joining online sessions). Carers will be advised to read each chapter of the educational booklet and supplementary website before the corresponding online support group session. The online support group sessions will run on ‘Zoom’, with a link and password to each session issued to carers before commencement. Carers will receive a reminder email two days before each online support group session. The research team will remain in contact with all participants to provide ongoing support with accessing the online support group sessions and supplementary website.

The nurse-led, online support group sessions will be delivered using an informal approach to facilitate a comfortable environment for the carers. Each session will consist of twelve carers and last approximately sixty minutes. The sessions will initiate with a standardised, educational presentation (approximately 20 minutes) on the allocated topic, with the remainder of the session (approximately 40 minutes) dedicated to questions raised during the session or submitted via the website; group discussion; tailored advice and signposting; and peer support. Carers will receive the option of having their cameras switched on or off during the sessions and will be encouraged to use the chat function to ask questions if unwilling to speak in front of the group.

Five programme rollouts of HELP (six weeks each) will be delivered across each of the three collaborating nations over a year period, with twelve carers per rollout (60 carers per nation; 180 carers in total). Rollouts will be separated by four-week windows, which will account for staff holidays and provide recruitment intervals for the subsequent rollout.

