### 2.3 Outcomes

An overview of the study flow and data collection process is presented in Fig 3. Guided by CFIR and NPT integration [13,14], quantitative (*i.e.,* questionnaires, logs, and checklists) and qualitative (*i.e.,* interviews) data will be collected across the participants at five time points: 1. Baseline, 2. Intra-intervention, 3. Post-intervention (six weeks), 4. Six months post-intervention, and 5. Study end (eighteen months). For questionnaire data, participants will have the option of completion via Microsoft Forms or telephone calls, depending on preference.

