#### 2.3.4 Participant outcomes.

The short and long-term impact of HELP on outcomes for carers and patients will be assessed across data from validated questionnaires, patient diaries, and medical records (see Table 2). Participant outcome data will be collected at three time points: 1. Baseline, 2. Post-intervention (week six), and 3. Six months post-intervention.

**Table 2 pone.0347037.t002:** Participant Outcomes and Measurement Instruments.

Sample	Outcome	Measurement Instrument	Time Point		
			Baseline	Post-Intervention (Week 6)	6 Months Post-Intervention
**Carers**	Carer Burden	Zarit Burden Interview, Short Form [26]	X	X	X
	Carer Preparedness	Preparedness for Caregiving Scale [27]	X	X	X
	QoL	12-Item Short Form Survey [28]	X	X	X
	Anxiety and Depression	Hospital Anxiety and Depression Scale [29]	X	X	X
	Stress	Perceived Stress Scale [30]	X	X	X
	Social Support	Multidimensional Scale of Perceived Social Support [31]	X	X	X
**Patients with HF**	Disease-specific, QoL	Minnesota Living with HF Questionnaire [32]	X	X	X
	Generic, QoL	EuroQoL Five Dimension Questionnaire [33]	X	X	X
	GP Visits with Reasons over Previous 6 Months	Bespoke, Recall Questionnaire at Baseline and Patient Diary Self-Completed from Baseline to 6 Months	X		X
	Most Recent LVEF Measurement	Medical Record	X		X
	Hospital Admissions with Reasons over Previous 6 Months	Medical Record	X		X

**Legend** QoL = Quality of Life; HF = Heart Failure; GP = General Practitioner; and LVEF = Left Ventricular Ejection Fraction.

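### As worded, Table 2 counts hospital admissions between baseline and the end of the six-week programme in neither of its two six-month windows

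*Protocol article*

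**What the plan says.** Section 2.3.4, Table 2, has a patient row headed "Hospital Admissions with Reasons over Previous 6 Months". The source is the medical record. The row is marked at baseline and at 6 months post-intervention; the week 6 column is blank.

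The same section gives the outcome time points as "1. Baseline, 2. Post-intervention (week six), and 3. Six months post-intervention". Section 2.3 lists the later points of the study as "3. Post-intervention (six weeks), 4. Six months post-intervention, and 5. Study end (eighteen months". Both lists treat the end of the programme and the six-month visit as separate occasions, the second dated from the first.

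Section 2.2.8 sets the programme length: "weekly online support group sessions are delivered to groups of approximately twelve carers over a six-week period". On timing before the first session, Section 2.2.9 says "Following recruitment, carers will be assigned a start date for HELP" and "One week prior to the first online support group session, carers will receive the educational booklet and access to the supplementary website". It does not say how long the wait is, or where in it the baseline assessment falls.

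The GP-visit row of Table 2 carries the same six-month label as the admissions row. Its follow-up source, however, is a diary that the patient keeps from baseline up to a point given only as 6 months.

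**The concern.** Two look-backs of six months, one ending at baseline and one ending six months after the programme, do not meet. The weeks left uncovered include the only weeks in which HELP is delivered. Nothing in the article says that admissions in those weeks are recorded elsewhere or are left out on purpose.

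Objective 3 is to explore the short and long-term impact on carers and patients, and the Discussion names fewer readmissions as a possible benefit. An admission during the programme, whichever way it points, would not appear in the results. Section 2.5.1 says that the outcome results will yield effect sizes for sizing a later definitive study, so the choice of window carries forward.

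Recruitment adds a reason to look closely: "Local cardiology teams will identify and approach potential participants during routine, in and out-patient HF appointments". For some patients the uncovered weeks may follow a recent acute episode, and there is no control group to show what would have happened anyway.

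**Working it through.** **Inputs.** Programme length 6 weeks (Section 2.2.8). Look-back 6 months at both extractions (Table 2), taken as 365.25 / 2 / 7 = 26.1 weeks. Final outcome visit 6 months after programme end (Sections 2.3 and 2.3.4). Materials issued 1 week before session 1 (Section 2.2.9). The time from baseline to session 1 is not stated, so it is varied; the 4-week value is an assumption.

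**Plan's own figure.** 5 rollouts × 12 carers × 3 nations = 180, as stated. It serves here only to give scale.

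**Feasibility of the reading.** Five rollouts with four breaks take 5 × 6 + 4 × 4 = 46 weeks. Adding 26.1 gives 72.1 weeks, inside the 78.3 weeks from 01/04/2026 to 01/10/2027. A visit six months after programme end therefore fits the calendar.

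**Windows.** Put baseline at week 0 and let w be the weeks from baseline to session 1.
- Baseline window: week −26.1 to week 0.
- Final visit: week w + 6 + 26.1.
- Follow-up window: week w + 6 to week w + 32.1.
- Uncovered gap: g = w + 6 weeks, a share g / (g + 26.1) of the time from baseline to final visit.

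| w (weeks) | Gap g (weeks) | Follow-up window (weeks) | Share uncovered |
|---|---|---|---|
| 0 | 6 | 6.0 to 32.1 | 6 / 32.1 = 18.7% |
| 1 | 7 | 7.0 to 33.1 | 7 / 33.1 = 21.2% |
| 4 (assumed) | 10 | 10.0 to 36.1 | 10 / 36.1 = 27.7% |

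**Events not counted.** The article gives no admission rate. For assumed constant rates r of 0.25, 0.5 and 1.0 per patient-year, and if all of the roughly 180 patients take part, a 6-week gap holds 180 × r × 42 / 365.25 = about 5, 10 and 21 admissions. The six-month window holds 180 × r × 0.5 = 22.5, 45 and 90.

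**Bias.** Let k be the admission rate in the gap divided by the rate afterwards. The rate seen in the follow-up window, divided by the true rate from baseline, is (g + 26.1) / (k × g + 26.1).

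| k (assumed) | g = 6 | g = 10 |
|---|---|---|
| 0.5 | 32.1 / 29.1 = 1.10 | 36.1 / 31.1 = 1.16 |
| 1 | 1.00 | 1.00 |
| 2 | 32.1 / 38.1 = 0.84 | 36.1 / 46.1 = 0.78 |

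The sign depends wholly on k, which the documents do not give. At k = 1 nothing is distorted, and only the events in the gap are lost.

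**The case against.** Six months before enrolment against six months after the programme is a legitimate comparison. The windows are equal in length, so raw counts compare directly, and leaving out the delivery period is a recognised choice when the question is what follows an intervention. This stands: the matched comparison need not be replaced or demoted. It does not explain why the programme weeks go unrecorded altogether.

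The window may also be loosely worded rather than fixed. The GP-visit row has the same label, yet its diary starts at baseline, and the interview text in Section 2.3.2 also says only 6 months. If the final point were counted from baseline, the gap would be zero. The extraction form is not shown. This lowers confidence in what was intended, but the Table 2 column heading and both lists of time points date the visit from the end of the programme. On either account the two rows need the same explicit dates.

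Admissions are one of several exploratory outcomes in a study that calls itself unpowered and non-definitive. The consequence is correspondingly modest, and the record will still hold the missing weeks.

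A reader might go further and infer that the plan understates follow-up admissions by some 16% to 22%, in favour of HELP. The documents do not support that. Those figures are the k = 2 row above, a single assumed rate ratio, with the upper one also needing an assumed four-week wait. Approaching some patients at in-patient contacts makes a raised early risk plausible, but the interval from such a contact to baseline is not stated.

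**Conclusion.** The point holds as one of coverage. On the wording of Table 2, admissions from baseline to programme end are counted in neither window: at least 6 of about 32 weeks (19%), 21% if baseline falls when materials are issued, and 28% under an assumed four-week wait. This rests on the six-month visit being dated from the end of HELP, which the text favours although the GP-visit row leaves some doubt.

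No direction or size of bias can be claimed. A change is still worth making before extraction begins, because Objective 3 cannot otherwise see admissions during delivery.

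**What to change.** In Table 2, define the follow-up extraction as every hospital admission, with its date and reason, from baseline to 6 months post-intervention. Give the GP-visit row the same start and end, stating that the diary runs to 6 months post-intervention.

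Keep the matched count of six months before baseline against six months after the programme. Beside it, report admissions per patient-month for the whole period from baseline, with any wait before session 1 and the six programme weeks shown separately, so that time before exposure to HELP is not mixed with time during or after it.

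Cost: a wider date range on a medical-record extraction that is already planned, with no added visit, plus whatever amendment approval Section 2.6 requires. If the diary was meant to stop six months from baseline, patients would keep it for somewhat longer. The full-period result must be a rate, because the windows are unequal and follow-up length varies with the start date. It does not fit the repeated measures analysis of variance in Section 2.5.1 and is best given as a description.

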#### 2.2.5 Patients.

Patients who are receiving informal support from the recruited carers will be invited to participate via the provision of data, which will allow their perspectives on HELP implementation to be captured, whilst also facilitating an assessment of the potential, dyadic impact of the intervention. These patients will be eligible to participate if they are: 1) Aged 18 years or older; 2) Physically and mentally able to engage comfortably in conversation and capable of reading written materials; 3) Clinically diagnosed with HF and receiving standard evidence-based HF therapies and either have HF symptoms or one episode of decompensation (symptoms requiring medical attention) in previous six months; 4) Able to speak and understand English; and 5) Receiving regular, unpaid support with managing their condition from a loved one (*i.e.,* a relative or spouse) or friend. Patients will be ineligible if their carers refused to participate in HELP. Carers will remain eligible for participation regardless of patient enrolment. One patient per carer will be invited to participate to enhance sample diversity (approximately 180 patients in total).

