### 2.4 Data management

Data management will comply with the requirements of the General Data Protection Regulation (2018). Personal data will be pseudonymised, with the master list linking participant identification numbers to personal information stored securely and separately from other data in a locked office within the School of Nursing and Midwifery, Queen’s University Belfast. A pseudonymised case report form (CRF) will serve as a consolidated resource documenting the data collected from each participant, with access limited to authorised individuals from the central research team at Queen’s University Belfast. These individuals will be responsible for data entry and validation at the point of entry into the CRF. Data from collaborating sites (*i.e.,* information from patient medical records) will be sent to the central research team via encrypted emails containing pseudonymised, password-protected data collection forms. Transcripts of audio-recordings will be pseudonymised, with transcription undertaken by a specialist service who has completed a data sharing and confidentiality agreement. All audio-recordings will be destroyed after the transcripts have been checked for accuracy. All paper data will be stored in a Master File and Site Files held within locked offices at the School of Nursing and Midwifery, Queen’s University Belfast and across the collaborating centres, respectively. All electronic data will be password protected and stored on an encrypted and password protected computer, inside a locked office at the School of Nursing and Midwifery, Queen’s University Belfast. On request, access to data will be granted for authorised representatives of the sponsor (Queen’s University Belfast) and regulatory authorities to facilitate study-related monitoring, audits, and inspections.

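### Hospital admissions rest on the site-supplied medical record alone, with no stated rule for the stay at which an in-patient is recruited, so the before-after comparison can show a fall without any effect of HELP

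*Protocol article*

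**What the plan says.** Section 2.3.4 states: "Participant outcome data will be collected at three time points: 1. Baseline, 2. Post-intervention (week six), and 3. Six months post-intervention". In Table 2, the outcome "Hospital Admissions with Reasons over Previous 6 Months" is marked at the first and third of these. The only instrument named is the medical record. GP visits, in the same table, are collected from patients by a "Bespoke, Recall Questionnaire at Baseline and Patient Diary Self-Completed from Baseline to 6 Months". No patient-reported source is listed for admissions.

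Section 2.4 explains that data from the collaborating sites, with medical record information as the example, "will be sent to the central research team via encrypted emails containing pseudonymised, password-protected data collection forms". How far that record reaches (one hospital, a group of hospitals or a region) is not stated.

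On recruitment, section 2.2.6 says: "Local cardiology teams will identify and approach potential participants during routine, in and out-patient HF appointments". Under section 2.2.5, patients qualify if they "either have HF symptoms or one episode of decompensation (symptoms requiring medical attention) in previous six months", so an admission is possible but not required. Section 2.5.1 analyses participant outcomes by repeated measures analysis of variance over time points. There is no control group.

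**The concern.** Two features act together.

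- **Reach of the source.** An admission to a hospital outside the site's record would not be counted, before or after HELP, and no second source would reveal it.
- **The recruiting stay.** A patient approached while in hospital carries that stay into the baseline look-back, and the site certainly holds it. Nothing equivalent is built into the follow-up window. The article gives no rule on whether the stay counts.

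With no control group, a baseline raised in this way appears as a fall after HELP. Section 3.0 names fewer readmissions as a hoped-for patient benefit. Section 2.5.1 will use the results as evidence of promise and to derive effect sizes for the sample size of a later study. An artefactual fall would overstate the promise and make that study too small. A larger sample would not remove it.

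**Working it through.** **The plan's own figures.** None is given for admissions: no expected rate, in-patient share or completeness of capture. The only figure to reproduce is the sample: 5 rollouts × 12 carers × 3 nations = 180 carers, with about 180 patients. It agrees with the article.

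**Model with no effect of HELP.** All three inputs are assumptions:

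- f = share of patients recruited during an admission that is then counted at baseline (range 0 to 0.5);
- λ = true other admissions per patient per six months, the same in both windows (range 0.2 to 0.6);
- c = share of those other admissions that the site record shows (range 0.6 to 1).

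Recorded admissions per patient:

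- baseline = f + λc
- follow-up = λc
- absolute fall = f
- relative fall = f / (f + λc)

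**Results over the ranges.**

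| f | Absolute fall per patient | Relative fall, smallest (λ = 0.6, c = 1) | Relative fall, largest (λ = 0.2, c = 0.6) |
|---|---|---|---|
| 0 | 0 | 0% | 0% |
| 0.10 | 0.10 | 0.10/0.70 = 14% | 0.10/0.22 = 45% |
| 0.25 | 0.25 | 0.25/0.85 = 29% | 0.25/0.37 = 68% |
| 0.50 | 0.50 | 0.50/1.10 = 45% | 0.50/0.62 = 81% |

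If all 180 patients took part, f = 0.25 would mean 0.25 × 180 = 45 recruiting stays in the baseline count.

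**Role of incomplete capture.** Take f = 0.25 and λ = 0.4:

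- c = 1: 0.65 to 0.40, a fall of 38%;
- c = 0.8: 0.57 to 0.32, a fall of 44%;
- c = 0.6: 0.49 to 0.24, a fall of 51%.

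The absolute fall is 0.25 each time. With f = 0 there is no change at any c. So incomplete capture that is equal in both windows gives no direction by itself; it only enlarges the relative fall once a recruiting stay is counted.

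**What each remedy does.** Perfect capture (c = 1) leaves the absolute fall at f. Leaving the recruiting stay out of the baseline count makes both windows λc, and the change is zero at every c.

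**Capture effect alone.** Suppose instead that true total admissions are equal in both windows, that a share s of the baseline total is recruiting stays (all captured), and that a share q of all others goes elsewhere. The recorded ratio is (1 − q) / [s + (1 − s)(1 − q)]. For q = 10%, 20% and 25%, s = 0.5 gives falls of 5%, 11% and 14%, and s = 0.1 gives 1.1%, 2.4% and 3.2%. At s = 0.5 this setting requires other admissions to double after recruitment, which nothing in the article supports. It therefore isolates the smaller component and is not an estimate of the total.

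**The case against.** A reader might infer that admissions elsewhere are missed, that the recruiting stay is always counted, and that follow-up must therefore look lower. The documents do not support that. The reach of the record is not stated, and if sites read a shared regional record, c is close to 1. No text says that the recruiting stay enters the baseline count. It can exist only for in-patient recruits, whose share is not given, and patients may qualify on symptoms alone. The same source and the same look-back apply at both times, so missing hospitals alone produce no fall. These objections stand, and the point is worded conditionally for that reason.

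It is also fair to say that a journal article may leave counting rules to the full protocol or to data collection forms not shown here. This applies to the rule on the recruiting stay, which may already exist. It applies less to the choice of source: Table 2 names an instrument for every outcome and gives GP visits two patient-reported sources but admissions none.

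Nor are admissions the only objective outcome, since ejection fraction also comes from the record. Admissions are one of eleven outcomes in Table 2, the article declares no statistical power, and section 3.1 says that the outcomes will not be definitive. This limits the consequence. That caveat cites the non-randomised design and the lack of power, however, and does not mention how admissions are captured or counted.

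Finally, self-report is not a complete answer. It leaves the recruiting stay in place, and it sets recall at baseline against a diary at follow-up where one source now serves both. The fix has to deal with both.

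**Conclusion.** The point holds in conditional form. Admissions outside the site record may be missed at both time points. If the recruiting stay of in-patients is counted, the uncontrolled comparison can show a fall with no effect of HELP. The absolute fall equals the in-patient share f, and incomplete capture enlarges it only in relative terms.

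The actual size cannot be derived from the documents. The tabulated figures rest on assumed values of f, λ and c, and on a background rate that is the same in both windows; a rate that rose after recruitment would make the net fall smaller. This bias is zero if no patient is recruited as an in-patient, or if the recruiting stay is left out. Selection of out-patients through a recent decompensation could also raise the baseline, but that is a separate matter, not quantified here.

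**What to change.** 1. Add one line for hospital admissions (hospital, date, reason) to the existing baseline recall form and patient diary. Let the diary cover the whole follow-up look-back. Table 2 does not say from when its six months run. If they run from baseline, the diary would stop at least six weeks before the look-back closes, because the programme itself lasts six weeks. Use the line to find admissions outside the site record. Report the combined count and the record-only count, since the latter uses the same source at both times. State in the plan how far the site record reaches.
2. Flag any admission ongoing at recruitment, and report the before-after comparison with and without it.

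The cost is one line on two existing forms, a slight burden for patients and some matching of reports to records. Baseline recall may be less complete than a diary, which could distort the combined count and is why the record-only count should stay. The change is easiest to make before data collection, which section 2.8 expects to start on 01/04/2026.
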